**Supplemental Material**  
**Statistical Analysis Plan (SAP) for**  
**SCORE Studies of Annual and Biannual MDA for *S. haematobium* in Niger**  
**Version 1.0, 3 January 2017**  
**Authors: the SAP-Niger Working Group**

## **PREFACE**

This statistical analysis plan (SAP) has been developed by SCORE team members to standardize the evaluation of outcomes data from SCORE urogenital schistosomiasis control studies in Niger. It provides guidance on appropriate data sources, variable definitions, and approaches for assessing quantitative outcomes. The intent is to provide consistent analysis of implementation and outcomes data for each arm of the study, and for the study overall. The data analysis plan presented below and in the Appendices is based on statistical methods that are available using SAS. Use of other statistical analysis packages is also appropriate.

The contents of this SAP represent a minimum analysis for this study. The tables described herein should be completed and provided to SCORE before the conclusion of the study for SCORE to use in reporting to the Bill & Melinda Gates Foundation (BMGF). They should be available for sharing upon appropriate request, e.g., as supplemental tables for publications. The choice of data to present in published papers is left to authors and will reflect country-specific needs and interests; however, the definitions and approaches described in this document should be used in analysis and published results should be consistent with those from the SAP analyses. In addition, investigators should review the guidelines from CONSORT (Campbell 2012) to ensure that they address all requirements for reporting randomized trials. Additional exploratory analyses beyond those described here are encouraged.

## I. STUDY ABBREVIATIONS AND BRIEF DEFINITIONS

CWT – Community-wide treatment

GEE - Generalized estimating equations

ICC – intra-class correlation

MDA – Mass drug administration delivered on an annual basis at a target dose of 40 mg/kg, with dose estimated from subject height using a dosing pole

SAC – School age children

SBT – School-based treatment

Sh – *Schistosoma haematobium*

SCORE — Schistosomiasis Consortium for Operational Research and Evaluation

SUDS — SCORE Uniform Data Set

Y — Year: Y1 data collection is defined as the baseline data collection, which occurs before treatment. Y1 treatment refers to the first MDA treatment

#### Abbreviations related to study arm treatment sequences

c — CWT

h- holiday

s — SBT

## **II. GOALS AND OBJECTIVES OF THE SCORE-ANNUAL VS. BIENNIAL *S. HAEMATOBII* TREATMENT STUDIES**

The overall goal of the SCORE project is to provide an evidence base and tools for programmatic decisions on how best to extend control of *Schistosoma* infections to achieve morbidity control, and, eventually, elimination. The SCORE-Gaining and Sustaining Control and Cohort studies are randomized trials designed to inform approaches to mass drug administration (MDA). These were developed through a collaborative process. The original harmonized protocols, which were to be followed by all groups funded to conduct this work, appear in Appendices A (Gaining and sustaining studies) and B (Cohort studies). Niger was to conduct a gaining, a sustaining, and a cohort study. A Standardized Analysis Plan (SAP) for these studies is available from SCORE upon request. However, because Niger did not follow the study protocol, the cohort study was discontinued, and the Niger study was redesigned in Year 3. The protocol for the redesigned Niger study is in Appendix C and a map of the redesigned study in in appendix X. This SAP has been developed for the redesigned Niger study.

### **a. Overview of SCORE-Niger MDA studies**

Niger was funded to conduct studies of urogenital schistosomiasis. Sh1 studies involved communities with prevalence during eligibility testing of <24%, and Sh2 studies involved communities with eligibility prevalence of  $\geq 24\%$ .

The original design of the Niger Sh1 and Sh2 gaining and sustaining control studies was predicated on the idea that randomization would result in starting prevalences being roughly equivalent in different study arms. However, because of the way in which Niger randomized its villages – with geographic clustering, starting prevalences were markedly different in the different arms, so that valid comparisons between arms could not be made.

### **b. Study design: Original design and the revised 2013 protocol**

**Intended design:** The Gaining and Sustaining studies are parallel cluster-randomized, open-label operational research trials of PZQ MDA for control of prevalence and intensity of *Schistosoma* infections in endemic communities in Africa.

For purposes of this protocol, a study community or village was required to have a primary school, because several arms of the study are school-based and every participating community must be eligible to be randomized to any of the study arms. However, a study community could have more than one school. If two nearby communities had schools with fewer than 100 children per school, but they were similar, they could be combined for purposes of this study and be considered as one study community.

Where schools had fewer than 100 schoolchildren aged 9-12 years, additional non-attending school aged children were recruited from the local villages. In the case of villages that shared water sources, one village was selected randomly to participate.

Prior to enrollment, village eligibility for either Sh1 or Sh2 in the original study design was determined by testing fifty 13-14 year-old children in each village. Once a village was enrolled in the study, the **primary outcomes of interest are prevalence and intensity among 9-12 year-old children**. A simple randomization procedure was used, without stratification. Re-randomization based on the first randomization results was not permitted.

In studies of communities with lower levels of *S. haematobium* prevalence (<24%, Sh1 studies), only SBT was implemented on an annual or every other year basis. The *original* study Sh1 had three desired study arms arranged as follows:

[figure not shown]

In studies of communities with higher levels of *S. haematobium* prevalence ( $\geq 24\%$ , Sh2 studies), either CWT or SBT was implemented on an annual or every other year basis. The *original* Study Sh2 had six desired study arms arranged as follows:

[figure not shown]

**Populations and expected sample size:** The goal of the study was to enroll 25 eligible villages per study arm, and to monitor each village's prevalence and intensity of *Schistosoma haematobium* infection among **a random sample of 100 resident 9-12 year-old children each year**, starting before implementation of MDA (Year 1) and continuing through Year 5 (see study arm schema above). Nominal enrollment for the Sh1 study was 75 villages, and for the Sh2 study, 150 villages, with to 10,000-22,500 children tested each year, according to schedule. (**N.B.** Communities assigned to 'holiday' were not tested in that year.) Because of the way in which Niger randomized its villages – with geographic clustering, starting prevalence was markedly different, so that valid comparisons between arms could not be made. Therefore, **the Niger study was re-designed.**

The failure to randomize appropriately was recognized following Y2 data collection, after two years of MDA. The current protocol is a BMGF-approved replacement for the previously approved protocol for gaining and sustaining studies. Within the following revised arms, randomization was carefully done at the *community*, not regional, level. The new study objective was to evaluate the impact of twice-a-year vs. once-a-year treatment with PZQ. Once-a-year and twice-a-year MDA, given in Years 3 and 4 of each study, were compared in the context of communitywide treatment (CWT) or school-based treatment (SBT) according the following revised schema:

- The previous Sh2 study Arms 1-3 are receiving CWT for the remainder of the study, starting with the 2013 MDA.
- Arms 4-6 from Study Sh2 and arms 1-3 from Study Sh1 from the original study design are receiving school-based treatment (SBT) for the remainder of the study, starting with the 2013 MDA.
- Within each arm, villages were randomized to receive either once or twice yearly treatment. Those with twice-yearly treatment will receive two MDA treatments during 2013 in June and December and two in 2014 in June and December.

[figure not shown][figure not shown][figure not shown]

In addition to 9-12 year-old children, SCORE studies included some data collection on first-year students and in adults. More information about data collected from these populations is provided in the protocols

and in Appendix D. Their results are not considered in this SAP, but may be used for future secondary analyses of the SCORE gaining and sustaining studies.

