### a. Individual-level data

Parasitological data on *Schistosoma* infection among children ages 9-12 were collected prior to each MDA and a year following the last treatment.

In the Sh control studies, 10 ml of urine from a single well-stirred urine sample for each individual was filtered twice, and each of these two filtrations was examined under the microscope; the number of eggs found in each slide and the corresponding volume of urine filtered was recorded.

Parasitological data were also collected in Years 1, 3, and 5 on children in the first-year class and in Years 1 and 5 on adults (see Appendix D). However, given that data on these populations do not represent the primary end-points of the SCORE treatment studies, and that the data collected on them are much more limited than that for 9-12 year olds, they will not be reported as primary end-points.

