### Figure 3. Intensity categories, by Arm, by Year.

This is a stacked bar chart, showing low, medium, and high intensity infections, by Arm, for Years 1-5, and each study separately. Intensity categories are defined as:

- Sh: Low 1-50 eggs/10 ml, high  $\geq 51$  eggs/10 ml

A supplemental table including the numbers used to make the chart should be available should modelers or other analysts want to use the exact data.

Table 4. Comparisons of prevalence and intensity at Year 5 among arms.

This table describes the primary outcomes.

|                         | Unadjusted prevalence model estimate (CI) | Adjusted prevalence model estimate (CI) | Unadjusted intensity ratio (CI) | Adjusted intensity ratio (CI) |
|-------------------------|-------------------------------------------|-----------------------------------------|---------------------------------|-------------------------------|
| Study A: Arm 1 v. Arm 2 |                                           |                                         |                                 |                               |
| Study B: Arm 1 v. Arm 2 |                                           |                                         |                                 |                               |
| Study C: Arm 1 v. Arm 2 |                                           |                                         |                                 |                               |

*General approach to analysis:* The general approach is to use mixed models to estimate differences between the arms in year 5 only, analyzing each study separately. We will report unadjusted estimates – with just village, study group and arm fitted in the model – and adjusted estimates – where sex and age are also included in the model. The mixed model will implicitly weight for any villages that were not able to sample 100 9-12 year old children.

ICC will be calculated using mixed models in the primary analysis.

All models will be based on individual level data on 9-12 year old children only.

*Sample code:* The following codes are provided as examples.

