**Supplemental Table S6:** Results for the modified Niger MDA trial, in which communities were randomized to receive once yearly or twice yearly praziquantel MDA for *S. haematobium* infection following an initial one or two rounds of SBT or CWT. Group A includes communities with microhematuria prevalence in eligibility testing of 5-20%. Groups B and C had prevalence in eligibility testing of >20%. See Figure 2 of the paper for study design details.

|                                                                          | Group A |         |         |         |              |              | Group B |         |         |         |              |              | Group C      |              |
|--------------------------------------------------------------------------|---------|---------|---------|---------|--------------|--------------|---------|---------|---------|---------|--------------|--------------|--------------|--------------|
|                                                                          | SSSS x1 | SSSS x2 | SHSS x1 | SHSS x2 | A1           | A2           | SSSS x1 | SSSS x2 | SHSS x1 | SHSS x2 | B1           | B2           | CCCC x1      | CCCC x2      |
| No. tested at baseline                                                   | 2,309   | 2,226   | 1,152   | 995     | 3,461 | 3,221 | 2,448   | 2,401   | 1,211   | 1,270   | 3,659 | 3,671 | 3,357 | 3,562 |
| No. infected at baseline                                                 | 108     | 120     | 21      | 28      | 129   | 148   | 533     | 573     | 365     | 252     | 898   | 825   | 480   | 834   |
| Prevalence at baseline (%)                                               | 4.7     | 5.4     | 1.8     | 2.8     | 3.7   | 4.6   | 21.8    | 23.9    | 30.1    | 19.8    | 24.5  | 22.5  | 14.3  | 23.4  |
| No. tested at Year 5                                                     | 2,440   | 2,476   | 1,270   | 1,172   | 3,710 | 3,648 | 2,432   | 2,463   | 1,189   | 1,277   | 3,621 | 3,740 | 3,689 | 3,724 |
| No. infected at Year 5                                                   | 20      | 7       | 2       | 2       | 22    | 9     | 396     | 300     | 443     | 203     | 839   | 503   | 425   | 392   |

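### The Niger once- versus twice-yearly models fit no pre-randomisation village prevalence or intensity, so they lose precision and are unprotected against chance imbalance, which is large in Study C

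*Combined protocol and SAP*

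**What the plan says.** Niger SAP, II.b. The faulty first allocation came to light late: "The failure to randomize appropriately was recognized following Y2 data collection, after two years of MDA". The replacement contrast covers later treatment only: "Once-a-year and twice-a-year MDA, given in Years 3 and 4 of each study, were compared". Allocation was at community level, and "Within each arm, villages were randomized to receive either once or twice yearly treatment".

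Niger SAP, I. Baseline keeps its old meaning: "Y1 data collection is defined as the baseline data collection, which occurs before treatment". Table 3 accordingly describes change from Year 1 to Year 5.

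Niger SAP, VI.b, general approach under Table 4. Studies A, B and C are analysed separately with mixed models on Year 5 data. The unadjusted model is described as "with just village, study group and arm fitted in the model"; the adjusted one adds sex and age. No sample model contains prevalence or intensity from Year 1, 2 or 3.

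Niger SAP, III.a. Earlier data should exist, since parasitological data on "infection among children ages 9-12 were collected prior to each MDA and a year following the last treatment". Villages on holiday were not tested that year (II.b), so Year 2 would have gaps, but II.b puts every group on treatment from the 2013 MDA.

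**The concern.** The Niger study was redesigned because, in the SAP's words on the first allocation, "starting prevalences were markedly different in the different arms". Having seen what unequal starting levels can do, one would expect the replacement analysis to carry a covariate for them. It does not.

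Village infection before treatment is likely to be a strong predictor of village infection at Year 5. Leaving it out widens every interval. If the draw happens to be uneven, the Year 5 contrast also absorbs the starting difference. At stake are both primary outcomes, prevalence and intensity, in a study where the reading of twice-yearly community-wide treatment could turn on this choice.

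**Working it through.** **Inputs.** Counts and community-level mean intensities (eggs per 10 ml) are from Supplemental Table S6; x1 is once yearly, x2 twice yearly. Everything is child-level and ignores clustering. Year 3 values are not in the documents, so Year 1 stands in for them.

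**1. Reproduce the table.** The S6 row "Prevalence at baseline" gives 14.3% and 23.4% for Group C. From the counts: 480/3357 = 14.3% and 834/3562 = 23.4%. Year 5: 425/3689 = 11.5% and 392/3724 = 10.5%. These agree.

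**2. Year 5 alone and relative to Year 1.** Let R1 and R5 be the x2/x1 ratios at Years 1 and 5, and s the share of the Year 1 log-ratio that persists to Year 5 without any treatment effect. The corrected ratio is R5 / R1^s. The present models correspond to s = 0; full carry-over is s = 1. The documents give no value for s.

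| Outcome, study | R1 | R5 (s = 0) | s = 0.5 | s = 1 |
|---|---|---|---|---|
| Prevalence, A | 4.59/3.73 = 1.23 | 0.42 | 0.37 | 0.34 |
| Prevalence, B | 22.47/24.54 = 0.92 | 0.58 | 0.61 | 0.63 |
| Prevalence, C | 23.41/14.30 = 1.64 | 0.91 | 0.71 | 0.56 |
| Intensity, A | 0.51/0.76 = 0.67 | 0.05/0.13 = 0.38 | 0.47 | 0.57 |
| Intensity, B | 5.10/4.11 = 1.24 | 1.39/3.61 = 0.39 | 0.35 | 0.31 |
| Intensity, C | 5.37/1.78 = 3.02 | 2.18/1.37 = 1.59 | 0.92 | 0.53 |

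In A and B every ratio stays well below 1. The A intensity means are very small and rounded, so that row is rough. In C the intensity ratio crosses 1 at s = ln 1.59 / ln 3.02 = 0.42.

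**3. How unusual is the Study C imbalance?** Take a design effect of 1 + 99 × ICC for 100 children per village. No ICC is given, so 0.02 to 0.30 is assumed. Pooled prevalence is 1314/6919 = 0.190 and the difference 0.0912. At ICC 0.10, SE = √(0.190 × 0.810 × 10.9 × (1/3357 + 1/3562)) = 0.031, so z = 2.9 (p = 0.003). At ICC 0.02, 0.20 and 0.30, z = 5.6, 2.1 (p = 0.03) and 1.7 (p = 0.08). Studies A and B give p ≥ 0.22 throughout.

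**4. Is the contrast biased?** A simulation of the re-randomisation with no treatment effect assumed 75 villages in three former arms (prevalence 8, 18 and 32%; between-village SD 1.0 on the logit scale).

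- Without a baseline term the mean log odds ratio was −0.005 (randomised within former arm) or 0.002 (pooled), with rejection rates of 3.2% and 4.8%. There is no bias over repeated allocation.
- Adding Year 1 prevalence cut the SD from 0.25–0.27 to 0.18. Against 0.25 that is (0.18/0.25)² = 0.52, about half the variance.
- Among draws with a Year 1 log-odds imbalance of 0.45 to 0.75 (Study C: ln 1.83 = 0.60), the model without baseline was off by about +0.39 and the adjusted model by about 0.

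**5. Does merging treatment histories matter?** The share of children in the sss group is nearly equal in x1 and x2 at Year 1 (A 66.7% and 69.1%; B 66.9% and 65.4%). Stratifying the Year 5 odds ratio on sss/shs moves it from 0.415 to 0.408 in A and from 0.515 to 0.506 in B.

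**The case against.** A reader might infer that the Niger contrasts are confounded by the known starting differences. The documents do not support that. Those differences separate the former arms and came from the geographically clustered first allocation. Once- versus twice-yearly treatment was allocated afresh, by community and within arm, so omitting a baseline costs precision and leaves a bad draw uncorrected but does not bias the design.

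A reader might also infer that merging former arms distorts the results. Studies A, B and C are kept apart, study group is in the models, and step 5 shows that the sss/shs split hardly matters. What remains open is which stratum was used. The sss:shs ratio of about 2:1 (A 4535/2147 = 2.1; B 4849/2481 = 2.0) suggests that sss holds two former arms, and Study C pools the former Sh2 Arms 1–3. But the SAP text does not define the coding of study group, and the redesigned protocol is only listed as an appendix.

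Third, the Year 1 label might seem to corrupt the primary result. It does not enter Table 4. Year 1 also precedes the re-randomisation, so it is a valid, if older, covariate. The label affects only descriptive change.

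Two cautions stand in full. The ratios relative to Year 1 rest on assumed carry-over through intervening treatment, and the value 1 is the far end of the range. Table S6 also reports results, so it can size the problem but cannot show that the plan was wrong when written.

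**Conclusion.** The point holds as one of precision and protection against chance imbalance. The randomised comparison is valid in expectation, and prespecifying a village baseline would have made it sharper and more robust.

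The practical weight falls on Study C. Its Year 5 prevalence ratio lies between 0.91 and 0.56, and its intensity ratio between 1.59 and 0.53, depending on how far the Year 1 difference persisted. The direction of the intensity result therefore depends on a choice that the SAP does not make. In Studies A and B the direction holds under either reading, and the prevalence ratios move little.

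This rests on unclustered child-level figures, on Year 1 standing in for Year 3, and on assumed values for carry-over, ICC and the simulation.

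**What to change.** 1. In all Niger Table 4 models, add village-level prevalence from the last survey before the Year 3 MDA, or from Year 1 if Year 3 is unavailable. For intensity, log(mean + a constant) is an alternative; the constant is needed because some villages may have no eggs.
2. Fit as the group term the stratum actually used in the 2013 allocation, and state its coding. Use one name in the code: the adjusted prevalence model calls it Group, and the adjusted intensity model leaves it off the CLASS line.
3. Show Year 3 beside Year 1 in Tables 1 and 3. Change from Year 1 includes the one or two MDA rounds given before the randomised contrast began.
4. Because results are already tabulated, report the added models beside the SAP's own and label them as added later.

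The cost is SAP wording, one covariate from surveys the SAP says were done, the stratum terms and extra table columns. In Study C that is about three degrees of freedom if the strata are the three former arms (two for strata, one for the covariate). Study A has only 22 + 9 = 31 positives at Year 5, so add nothing there beyond the single baseline covariate and the stratum.

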### c. Limitations to the analyses included in this SAP

- Adverse events during MDAs were recorded by those administering the drugs in a manner consistent with WHO or country guidelines. These records were not requested as part of the SCORE research. Therefore, the planned SAP analyses do not include a “safety” component.
- Cost data collected in Year 2 were also impacted by the failure to randomize appropriately and are not considered further.

## III. DATA COLLECTION, AND TYPES OF DATA AVAILABLE

The table in Appendix D describes the data elements available from the SCORE-Niger Study.

### a. Individual-level data

Parasitological data on *Schistosoma* infection among children ages 9-12 were collected prior to each MDA and a year following the last treatment.

In the Sh control studies, 10 ml of urine from a single well-stirred urine sample for each individual was filtered twice, and each of these two filtrations was examined under the microscope; the number of eggs found in each slide and the corresponding volume of urine filtered was recorded.

Parasitological data were also collected in Years 1, 3, and 5 on children in the first-year class and in Years 1 and 5 on adults (see Appendix D). However, given that data on these populations do not represent the primary end-points of the SCORE treatment studies, and that the data collected on them are much more limited than that for 9-12 year olds, they will not be reported as primary end-points.

